## Abstract

**Background:**

Osteoarthritis (OA) is one of the most common disabilities in the elderly. When conservative management fails, total joint arthroplasty (TJA) is the treatment of choice for end-stage OA. Since quality and durability of implants has steadily improved, pre -and postsurgical processes moved into the focus of research. Hence, eHealth approaches offer an opportunity to provide a more available continuity of care. Regarding individualized pre-, peri-, and postsurgical stages, eHealth is expected to improve patient engagement, self-care, and outcomes across the surgical pathway. Aim of this study is to evaluate the effectiveness of the eHealth application “alley” as an adjuvant intervention to TJA. The app provides comprehensive information to empower patient with hip or knee OA to prepare and accompany them for their TJA surgery. Our primary hypothesis is that the pre- and postoperative adjuvant use of the eHealth application “alley” (intervention group, IG) leads to improved functional outcome.

**Methods:**

Prospective, randomized, controlled, multi-center trial including *n* = 200 patients diagnosed with hip and *n* = 200 patients with knee OA (*n* = 200) scheduled for TJA. Patients of both groups will be randomly assigned to one of two study arms. Patients in the intervention group will receive access to the functions of the “alley” app. The app presents informative (e.g., information about osteoarthritis), organizational (e.g., information about medical rehabilitation), and emotional/empowerment (e.g., information about the relationship between mood and pain) content. Patients evaluate their condition and functional level by means of standardized digitally questionnaires. Patients in the control group will not receive any functions of the app. Assessments will be performed at baseline before, 10 days after, 1 months after, 3 months after, 6 months after, and 12 months after TJA. Primary outcome is change from baseline measured by the Hip Osteoarthritis Outcome Score or Knee injury and Osteoarthritis Outcome Score 3 months after TJA. The statistical analysis (*t*-test for independent variables with effect size Cohen’s *d*) is performed separately for patients with TKA and THA.

**Discussion:**

Overall, the study aims to improve the understanding of the benefits of eHealth applications in the treatment of elderly patients with knee or hip arthroplasty. The approach is novel since a health care companion is combined with a digital information platform enabling direct and continuous feedback from the patients to the therapeutic treatment team. As the study investigate the effectiveness under everyday conditions, it is not feasible to control whether the patients in the IG read the educational information of the app respectively the control group consume additional information from other sources. However, this increases the external validity of the study if significant effects for the app can be demonstrated.

**Trial registration:**

German Clinical Trials Register: DRKS00025608. Registered on 21 June 2021.

## Administrative information

Note: The numbers in curly brackets in this protocol refer to SPIRIT checklist item numbers. The order of the items has been modified to group similar items (see http://www.equator-network.org/reporting-guidelines/spirit-2013-statement-defining-standard-protocol-items-for-clinical-trials/).

## Introduction

### Background and rationale {6a}

Osteoarthritis (OA) is one of the most common disabilities in the elderly. With a lifetime risk of 25% in the population aged 85 years, symptomatic hip OA represents one of the most prevalent diseases [1]. Similarly, the prevalence of knee OA increases with age and can be detected in up to 44% in subjects older than 80 years [2]. OA is a heterogeneous disease evoked by several causes, including local and systemic, genetic, and environmental factors, and is consequently difficult to prevent [3, 4]. When conservative management fails, total joint arthroplasty (TJA) is the treatment of choice for end-stage OA to reliably relieve pain and restore joint function [5, 6]. TJA is considered to be one of the most successful surgical procedures, while it has been shown as a cost-effective intervention for patients who do not benefit from conservative approaches [7]. Worldwide, more than 1 million TJAs are implanted annually [8], and it is expected that in future the number of surgeries will further increase due to demographic changes [3, 9].

Since the quality and durability of implants has steadily improved over decades, the pre -and postsurgical processes moved into the focus of research in order to achieve potential improvements. For instance, the optimal care after hospitalization has not yet been determined and shows a broad variety of treatment [10]. From diagnosis, therapy and rehabilitation to aftercare, patients have intensive contact with various actors of the health care system. This patient’s “journey” often extends over years and entails several loops within the health sector, resulting in high costs and diverse short and long-term results. Process optimization pathways in health care represent a possibility with great economic leverage. Moreover, these improvements may enhance process outcomes and thereby enable long-term savings. Current literature identified options for improving specific parts of the patient`s journey, e.g., patient satisfaction as quality indicator of healthcare or patient adherence [11, 12]. Further studies specified patient education as distinct option for optimizing patient pathways, while preoperative education and knowledge showed positive effects regarding adverse events, cost-effectiveness, and pain and function after TJA [13] as well as improved outcomes and reduced hospital stay [14, 15]. In order to achieve an implementation in clinical routine, eHealth approaches are currently being deployed, e.g., to address patient education with regard to TJA [16]. EHealth, defined as “the use of information and communication technologies for health” by the WHO [17], offers an opportunity for health professionals to provide an enhanced and more available continuity of care to serve the patients individual needs [18]. Digital interventions can be constantly updated, have the potential to increase patient engagement, enhance patient recovery, and reduce potential postoperative complications [16]. In addition, eHealth may improve cost-effectiveness as patients can receive time- and space-independent support before and after treatment [19, 20, 21]. Regarding individualized pre-, peri-, and postsurgical stages, eHealth is expected to improve patient engagement, self-care, and outcomes across the surgical pathway [18].

### Objectives {7}

Aim of the study is to evaluate the effectiveness of the eHealth application “alley” as an adjuvant intervention to total joint arthroplasty (TJA) as current gold standard of treatment in patients with knee and hip OA scheduled for surgery. In the presented study design, these two indications will be investigated independently of each other. Nevertheless, for both patients’ groups data collection is carried out via “alley” application. Accordingly, the primary outcome is change from baseline in the functional status measured with the total scores of the Hip Osteoarthritis Outcome Score (HOOS) for patients scheduled for total hip arthroplasty (THA) and the Knee injury and Osteoarthritis Outcome Score (KOOS) for patients scheduled for total knee arthroplasty (TKA).

The primary hypothesis is that the pre- and postoperative adjuvant use of the eHealth application “alley” (intervention group, IG) leads to improved functional outcome 3 months after TJA in patients with knee or hip OA compared to their equivalent control group (CG) that did not use the application. In this research, the overall effect of the application as complex intervention will be evaluated as standalone entity. Individual sub-questions on the subject of health literacy or in which format information should be administered to patients are not evaluated. Our secondary hypotheses are that the eHealth application will further improve pain, quality of life, depression and anxiety, optimistic mood, and risk of falling.

### Trial design {8}

The trial is planned as a prospective, randomized, controlled, non-blinded multi-center study to compare “alley” with standard treatment with scope of a superiority study design in two independent indications. Two hundred patients scheduled for THA and 200 patients scheduled for TKA will be independently randomly assigned to the IG or CG. Assessments will be performed at baseline before TJA (*t*_0_), 10 days after TJA (*t*_1_), 1 months after TJA (*t*_2_), 3 months after TJA (*t*_3_), 6 months after TJA (*t*_4_), and 12 months after TJA (*t*_5_).

## Methods: participants, interventions, and outcomes

### Study setting {9}

The study will be conducted in eight clinical sites in Germany. A total of two academic hospitals and six community clinics participate in the study. The full list of these clinics can be obtained via German Clinical Trials Register (https://www.drks.de/) under the registration code DRKS00025608.

### Eligibility criteria {10}

Patients presenting at one of the study sites with the indication for knee or hip replacement who are scheduled for TJA will be screened for inclusion and exclusion criteria. The screening is usually performed by the physician in charge during the consultation. Study inclusion is permitted with a signed informed consent form. Inclusion and exclusion criteria are displayed in Table 1.

**Table 1 Tab1:** Inclusion and exclusion criteria of the alley app trial

**Inclusion criteria**	
1. Scheduled hip or knee arthroplasty 2. (OPS code 5-820/5-822)	
3. Both gender the ages older than 18 years	
4. Ownership of a smartphone or internet-enabled device (e.g., tablet)	
**Exclusion criteria**	
1. Knee or hip arthroplasty due to emergency (e.g., after a fall)	
2. Knee or hip arthroplasty due to revision surgery	
3. Level 3 care degree or higher according to the German long-term care insurance	
4. Cognitive impairment of any kind (according to the assessment of the attending physicians) that prevents the proper use of the app	
5. Neurological disorder (e.g., Parkinson’s disease, MS, dementia) (according to the assessment of the treating doctors) that prevents the proper use of the app	
6. Severe psychiatric disorder that prevents the proper use of the app.	
7. Patient’s age younger than 18 years	
8. Insufficient knowledge of German language to use the app	
9. No ownership of a smartphone or internet-enabled device	
10. Women in pregnancy	
11. Women during lactation	

### Who will take informed consent? {26a}

During the first ambulatory visit, patients are verbally informed about the study by the attending physician in conjunction with a written patient information. At this point, the patients are already screened and assigned to the CG or IG by means of randomization. After this visit, patients have time to consider participation until the next mandatory pre-stationary consultation (1 to 2 weeks before surgery). In case of study participation, the group allocation remains. If a decision is made against participation, the allocation is canceled.

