### Outcomes {12}

Standardized and self-constructed questionnaires are applied to operationalize the target criteria. After registration with alley, all patients undergo an onboarding process, in which patients complete the medical questionnaires. In total, patients are surveyed at six measurement time points: Baseline before the surgery (*t*_0_) and 10 days after surgery (*t*_1_) as well as 1 (*t*_2_), 3 (*t*_3_), 6 (*t*_4_), and 12 months (*t*_5_) after TJA.

The primary outcome is change from baseline in functional status measured by the Hip Osteoarthritis Outcome Score (HOOS) or Knee injury and Osteoarthritis Outcome Score (KOOS) 3 months after TJA. The statistical analysis will be carried out separately for the two medical indications. Further secondary endpoints of the study are depression, anxiety, physiological, mental, and social health, pain, risk of falling, dispositional optimism and pessimism, patients’ expectation, post-operative complications, satisfaction with treatment, perceived knowledge of the patient about the disease, and health literacy. The secondary endpoints will also be analyzed separately for patients with hip and knee complaints. An overview of the instruments and measurement times is given in Table 2.

**Table 2 Tab2:** Target criteria, assessment instruments, and measurement time points

Target criteria	Assessment instruments	Measurement time points					
		***t***_***0***_	***t***_***1***_	***t***_***2***_	***t***_***3***_	***t***_***4***_	***t***_***5***_

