### Assignment of interventions: allocation

#### Sequence generation {16a}

A 1:1 randomization has been conducted, assigning patients to either CG or IG for THA or TKA, respectively. For this purpose, two randomization lists have been created using Excel random number generator, creating separate lists for THA and TKA. These lists contained a predefined identification code for each indication, which was randomly assigned to the IG or CG. If patients agreed to participate, they were assigned to this list and thus received a unique identification code. This personal code serves as login for the “alley” application. As the randomization list was a shared online document for all study sites, simultaneous double submissions had to be avoided. For this reason, block randomization has been used for blocks of 50 patients. This means that each of the eight study sites is allocated to a fixed slot of 50 patients on the randomization list. During patient recruitment, these slots are successively filled. If more than 50 patients are to be recruited, new slots can be released at the end of the list. The randomized allocation of patients to either IG or CG allows minimizing the inclusion of patients with strong affinity for using digital applications in the IG. Randomization will ensure an equal distribution of patients.

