#### Implementation {16c}

Physicians make use of the pre-randomized lists and allocate patients to the next unused slot, starting from the top. The assignment to either IG or CG is performed during consultation. After screening and handing out study information, the patient is directly allocated to IG or CG by the physician. For this purpose, the physician accesses the secure online “container,” selects the next free slot with an ID code in the randomization list, and assigns it to the patient. The extracted ID code must be entered in the alley application via installation and indicates to which group the patient has been assigned to. After this outpatient clinic appointment, patients have time to decide whether they want to participate till the next consultation (approx. 14 days before surgery). In the case of study participation, the group allocation remains; otherwise, the ID will be removed.

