#### Methods in analysis to handle protocol non-adherence and any statistical methods to handle missing data {20c}

The allocation of patients to the IG and KG is realized via an individual ID, which can only be assigned once. Once the patient enters the ID received from the attending physician into the alley application, the patient is clearly assigned to one of the two groups. Accordingly, protocol errors regarding randomization are not to be expected. Further, it is not possible to verify whether the patients of the IG are reading the provided digital information. Feedback on the usefulness of the application is only provided indirectly by physicians and patients themselves during the survey.

As this trial uses an online survey, missing data within one questionnaire is not possible. If a survey is not completed at a measurement point, the existing data will be used for the evaluation. Generally, an intention-to-treat (ITT) analysis as well as a per protocol (PP)-analysis will be performed. However, the PP analysis is used exclusively to validate the ITT analysis. To address our research question, the main analyses are carried out exclusively by means of ITT.

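### Patients are allocated before they decide on participation and decliners' allocations are cancelled, so the set called ITT is open to selection by arm; baseline is also self-reported after allocation

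*Protocol article*

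**What the plan says.** Two sections of the protocol article put allocation before the decision to take part.

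- Who will take informed consent? {26a}, on the first ambulatory visit: "At this point, the patients are already screened and assigned to the CG or IG by means of randomization". The patient then has until the consultation 1 to 2 weeks before surgery to decide. For those who decline: "If a decision is made against participation, the allocation is canceled".
- Implementation {16c}: "After screening and handing out study information, the patient is directly allocated to IG or CG by the physician". After the reflection period: "In the case of study participation, the group allocation remains; otherwise, the ID will be removed".

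Sequence generation {16a} gives the other order: "If patients agreed to participate, they were assigned to this list and thus received a unique identification code".

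On who knows the arm, Concealment mechanism {16b} says that treating physicians did not know the group at recruitment. The same section lists group affiliation among the fields of the shared list. {16c} has the physician open that list, take the next free slot, and pass on an ID that indicates the group when it is entered at installation. Under {17a}, neither patients nor staff are blinded.

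On baseline, {16a} makes the personal code the app login, and Outcomes {12} says: "After registration with alley, all patients undergo an onboarding process, in which patients complete the medical questionnaires". The primary outcome is the change in HOOS or KOOS from that baseline to 3 months. On the analysis set, section {20c} says that "the main analyses are carried out exclusively by means of ITT".

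**The concern.** Randomisation protects the comparison only for everyone who was randomised. If patients can leave between the draw of the ID and the count of participants, and if they or their physician know the arm by then, willingness to stay can differ by arm. The control offer is questionnaires in an app without its functions, so unequal refusal is plausible. An ITT label cannot repair this, because removed patients have no outcome data. Removing their IDs also discards the record that would show whether refusal was unequal.

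The second part concerns the baseline. The planned test compares change scores, so an arm-related shift in the self-reported baseline passes one-for-one into the estimated difference. This matters because the article's Strengths and limitations section rests its attribution of HOOS/KOOS differences to the app on the randomised design.

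**Working it through.** **Order of steps.** The article gives no figure to reproduce for this point, so the first check sets the sections side by side.

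| Section | Order stated |
|---|---|
| {26a} | information and allocation at first visit → decision → decliner's allocation cancelled |
| {16c} | screening, information, allocation → decision → decliner's ID removed |
| {16a} | agreement → assignment to list and ID |
| {16a} and {12} | ID → app login → baseline questionnaires |

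The first two rows agree with each other and contradict the third. The requirement of signed consent for inclusion (Eligibility criteria {10}) does not settle the matter, because it does not say whether the ID is drawn before or after signature. The last row holds under either order: the login is the allocated ID, so baseline always follows allocation.

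**Possible size (assumed inputs).** The article gives an SD of 15 points, a planned difference of 9 points, 61 per group at 3 months and 100 per group recruited. The 61 is used here only as the planned number analysed. Refusal shares and outcome differences are not in the article, so they are assumptions.

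If a share p of allocated control patients declines, with mean change D, and those who stay have mean change S, the control mean among all allocated is (1 − p)S + pD. The analysed control mean is S. The shift is therefore S − [(1 − p)S + pD] = p(S − D). Assume no refusal in the app arm.

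- p = 0.15, |S − D| = 5: 0.15 × 5 = 0.75 points, 8% of the planned 9.
- p = 0.20, |S − D| = 8: 0.20 × 8 = 1.6 points, 18% of the planned 9.

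Standard error of the difference: 15 × √(2/61) = 2.72, or 15 × √(2/100) = 2.12. With bias b and no true effect, the two-sided error is Φ(−1.96 + b/SE) + Φ(−1.96 − b/SE). The first term is the tail on the side of the bias, the second the opposite tail.

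| n per group | b | b/SE | tail on side of bias | opposite tail | two-sided error |
|---|---|---|---|---|---|
| 61 | 0.75 | 0.28 | 4.6% | 1.3% | 5.9% |
| 61 | 1.6 | 0.59 | 8.5% | 0.5% | 9.1% |
| 100 | 0.75 | 0.35 | 5.4% | 1.0% | 6.4% |
| 100 | 1.6 | 0.75 | 11.4% | 0.3% | 11.7% |

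**Direction.** If control decliners would have improved less than stayers (D < S), removing them raises the control mean and the bias works against the app. False significance for the app then falls from 2.5% to the opposite-tail column. If they would have improved more (D > S), the bias favours the app, and the side-of-bias column applies.

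**Second illustration.** Let the consent decision be a latent normal variable correlated with the outcome. Consent of 90% in both arms with equal selection gives no bias. Consent of 90% in the app arm and 70% in control, with correlations of 0.1 to 0.5, gives an absolute bias of 0.5 to 2.3 points and a two-sided error of 5.3% to 13.1% at 61 per group.

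**The case against.** The strongest objection is that cancelling allocations biases the comparison only if the decision to decline depends on the arm. {16b} says physicians did not know the group at recruitment. {17a} says patients recognise their arm by receiving educational content or only questionnaires, which could mean after they start using the app. If both hold, refusal cannot depend on the arm and the consenting patients remain comparable. By the same reading, baseline answers given at onboarding could precede awareness of the arm. The 150 EUR payment and later control access to the content may also dampen unequal refusal.

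Part of this stands. A reader might infer that the analysed set has in fact been selected by arm. The article does not support that: it reports no refusals by arm and does not fix the moment of disclosure. A reader might also infer that the bias flatters the app, but its direction depends on who declines. Likewise, baseline after allocation is established; baseline after the patient knows the arm is not.

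The objection does not remove the point. The statement about physicians conflicts with a list that shows group affiliation and an ID that indicates the group, both handled by the physician at that same consultation. The article therefore cannot be relied on to show that the arm was hidden until the decision.

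**Conclusion.** The concern holds in this form. As described in {26a} and {16c}, randomised patients who decline are left out of the set called ITT, and that set is open to selection by arm if the arm is known before the decision. {16a} contradicts this order, and {16b} is inconsistent with its own list and with {16c}. Under either order, the baseline of the change-from-baseline endpoint is self-reported after allocation in an open-label trial.

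Confidence is high for the order of steps and for the contradictions. The size and direction of any bias are unknown. The figures of about 6–9% two-sided error at 61 per group and 6–12% at 100 per group rest on assumed refusal of 15–20% in the control arm only, and on assumed differences of 5–8 points between stayers and decliners. With equal refusal and equal selection in both arms, the bias is zero. The point still needs correction, because the procedure permits the bias and removes the record needed to detect it.

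**What to change.** Reconcile {26a}, {12}, {16a}, {16b} and {16c} to one order: signed consent, then the baseline questionnaires, then drawing of the ID and disclosure of the arm. Keep the next allocation hidden from the physician until that draw; the shared list should not show group affiliation for unused slots. Baseline must then be possible in the app before the arm-specific ID is entered. Never remove or reissue a drawn ID.

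The Trial status section dates recruitment to 2021–2022, so reordering may come too late for many or all patients. For those already allocated before consent, keep the cancelled IDs with arm and site, report refusals by arm in the flow chart for hip and knee separately, and describe the analysed set as allocated patients who consented, not as unqualified ITT. State when patients and physicians learned the arm.

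The cost is a reordering of visit steps and a change to the list and the app login. Patients who use the full reflection time would start the app somewhat later before surgery; those ready to consent at the first visit lose nothing. The reporting part needs only that the cancelled entries are retained.
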